## Abstract

**Background:**

Sufficient physical activity and a limited amount of sedentary behaviour can prevent a range of chronic diseases. However, most adults do not meet the recommendations for physical activity and sedentary behaviour. Effective and engaging interventions are needed to change people’s behaviour. E- and m-health interventions are promising, but unfortunately they result in small effects and suffer from high attrition rates. Improvements to intervention content and design are required. Qualitative research has revealed the need for clear and concise interventions. Furthermore, many interventions use a range of behaviour-change techniques, and it is yet unknown whether these techniques are equally important to obtain behaviour change. It may well be that a limited set of these techniques is sufficient. In this study, the aim is to experimentally investigate the efficacy of three behaviour-change techniques (i.e. action planning, coping planning and self-monitoring) on physical activity, sedentary behaviour and related determinants among adults.

**Methods:**

In a 2 x 2 x 2 factorial trial participants will be randomly allocated to eight groups (including one control group). Each group will receive a different version of the self-regulation-based e- and m-health intervention ‘MyPlan 2.0’, in which three behaviour-change techniques (i.e. action planning, coping planning, self-monitoring) will be combined in order to achieve self-formulated goals about physical activity or sedentary behaviour. Goal attainment, and levels of physical activity and sedentary behaviour will be measured via self-report questionnaires.

**Discussion:**

This study should provide insight into the role of various behaviour-change techniques in changing health behaviour and its determinants. Its experimental and longitudinal design, with repeated measures of several determinants of behaviour change, allows an in-depth analysis of the processes underlying behaviour change, enabling the authors to provide guidance for the development of future e- and m-health interventions.

**Trial registration:**

This study is registered as MyPlan 2.0 as a clinical trial (ID number: NCT03274271). Release date: 20 October 2017.

**Electronic supplementary material:**

The online version of this article (10.1186/s13063-019-3456-7) contains supplementary material, which is available to authorized users.

## Background

Sufficient physical activity (PA) and limited sedentary behaviour (SB) may reduce adverse health outcomes such as cardiovascular diseases, diabetes type 2, depression and cancer [1–7]. Physical activity is defined as ‘any bodily movement produced by skeletal muscles that requires energy expenditure’ [8]. The level of energy expenditure is expressed in metabolic equivalents (METS). Three levels of PA are defined based on these METs; ‘light-intensity physical activities’ such as doing the dishes or standing at your desk, ‘moderate-intensity physical activities’ such as cleaning windows or cycling to work and ‘vigorous-intensity physical activities’ such as running or chopping wood [9]. Given the examples above, PA means more than ‘exercise’ alone. For adults, it is recommended to be physically active at moderate to vigorous intensity (MVPA) for 30 min each day [10]. However, 31.1% of the worldwide population is physically inactive, with even higher levels of inactivity in higher-income countries [11]. Sedentary behaviour is defined as ‘any waking behaviour characterised by an energy expenditure ≤ 1.5 METs while in a sitting, reclining or lying posture’ [12]. For example, activities such as working at the computer while sitting, watching television or driving a car are considered SBs; however, sleeping is not. For SB, only a few countries have developed recommendations. In Belgium, for example, the ‘Flemish Institute for a Healthy Living’ (Vlaams Instituut Gezond Leven) recommends that adults limit prolonged periods of sitting and interrupt sitting time every 20–30 min [13]. Nevertheless, adults in Belgium sit on average 8.3 h per day [14]. Across Europe, adults report more than 5 h of sitting per day, with 18.5% sitting more than 7.5 h per day [15]. Consequently, there is a strong need for effective interventions that promote PA and limit SB on a large scale.

E- (electronic) and m- (mobile) health is defined as ‘the use of information and communications technology, especially the Internet, to improve or enable health and health care’ [16]. E- and m-health interventions have the potential to reach large groups in an interactive way [17, 18]. Furthermore, they are effective in changing health behaviours such as PA and SB [19–22]. Although these interventions are promising, effect sizes are often small and high attrition rates (60–80%) are observed [21, 23]. There is a need to improve e- and m-health interventions and to engage users for a sufficiently long time in order to induce long-term behavioural change.

To improve users’ engagement, interventions may be tailored to the specific needs of the users and only contain personally relevant information [24, 25]. Furthermore, e- and m-health intervention sessions should be clear and concise [26]. It is important that interventions offer effective and sufficient content in order to establish behaviour change. Informed by theoretical models of behaviour change (for example: the Health Action Process Approach (HAPA) [27]), interventions often include several behaviour-change techniques such as action planning, coping planning, prompting self-monitoring of behaviour, etc. [28]. The effectiveness of these techniques is well-established [29–31], but including various techniques increases the risk of making the sessions time-consuming and less engaging for the users. Up to now, it is unknown whether these techniques are equally important to obtain behaviour change, or whether a limited set of these techniques is sufficient. Gaining insight into the efficacy of different behaviour-change techniques can provide guidance in removing particular behaviour-change techniques in order to create more efficient interventions [32]. Therefore, studies using an experimental approach are greatly needed [33–36]. The publication of research protocols is essential to avoid publication bias and outcome reporting bias [37]. In this paper we report our research protocol taking into account the Standard Protocol Items: Recommendations for Interventional Trials (SPIRIT) guidelines [38]. The completed SPIRIT Checklist has been included as Additional file 4 and the SPIRIT Figure can be found in Fig. 3.

## Aims and objectives

Our primary aim is to investigate which combination of behaviour-change techniques of an e- and m-health intervention in adults results in an optimal efficacy. We will explore the role of three behaviour-change techniques (i.e. action planning, coping planning and self-monitoring) on PA, SB and the attainment of self-formulated goals. We will apply an experimental approach and conduct a 2 x 2 x 2 factorial randomised trial using ‘MyPlan 2.0’, an e- and m-health intervention to increase PA and to reduce SB among adults.

Our second aim is to investigate the effect of the self-regulation techniques on mediating change-related determinants (i.e. self-efficacy, motivation, intention, action planning, coping planning, self-monitoring, risk perception and outcome expectancies) and to examine possible moderating effects of demographic variables. Hypotheses about mediation and moderation are informed by the HAPA [27, 39, 40], a self-regulation model that includes both pre-intentional as well as post-intentional determinants of behaviour change.

Our third aim is to investigate whether our intervention is effective for particular groups of participants. According to the HAPA model, individuals can be divided into three groups, based on their ‘mindset’ regarding behaviour change. The first group or ‘pre-intenders’ consists of individuals that have not yet formed an intention. The second group or ‘intenders’ have formed an intention to change their behaviour, but they do not yet perform the action itself regularly. The third group or ‘actors’ already perform the action for which they previously formed an intention. Interventions can be tailored upon these different mindsets, hence targeting mostly pre-intentional or post-intentional determinants. Because our intervention focusses on bridging the intention-behaviour gap, we expect that our intervention works better for intenders than for pre-intenders and for actors.

## Methods

### Study design

The design of the study is a 2 x 2 x 2 factorial randomised trial, in which participants are randomly allocated to eight different groups (including one control group). Each group will receive a different version of the e- and m-health intervention, in which three different behaviour-change techniques (i.e. action planning, coping planning, self-monitoring) are combined. The control group will receive only tailored feedback, information and tips and tricks. Table 1 shows the combination of the techniques within each of the groups.

**Table 1 Tab1:** Behaviour-change techniques provided for each group

	Action planning	Coping planning	Self-monitoring
Group 1	+	+	+
Group 2	+	+	–
Group 3	+	–	+
Group 4	–	+	+
Group 5	+	–	–
Group 6	–	+	–
Group 7	–	–	+
Group 8 (control group)	–	–	–

### Intervention

Each group will receive a different version of the e- and m-health intervention MyPlan 2.0. MyPlan 2.0 is based upon a previous e-health intervention, called ‘MyPlan 1.0’, which was systematically developed using the intervention mapping protocol [41]. MyPlan 1.0 is a web-based intervention to promote PA and fruit and vegetable intake in the general population, and has been tested in general practice. The programme has shown to be effective in improving healthy behaviour [42–44]. However, high attrition rates were observed and researchers experienced problems with the implementation by general practitioners [42–44]. Therefore, the programme has been further developed into MyPlan 2.0, which participants can use autonomously at home. In order to increase engagement, different adaptations were made based on quantitative and qualitative research [24, 26, 45–47]. MyPlan 2.0 consists of a website (www.mijnactieplan.be/meerbewegen) as well as a mobile application (app). It aims to increase PA and decrease SB in the general adult population (MyPlan 2.0 is also used for another independent study in our research group, which focusses on adults with diabetes mellitus type 2 [48]). The website consists of five weekly sessions, whereas the app offers daily support. Similar to MyPlan 1.0, MyPlan 2.0 is based on self-regulation theory [49, 50] and includes various self-regulation-based behaviour-change techniques [28, 51] in order to bridge the intention-behaviour gap [27, 52, 53]. In both the website and the app, the techniques can easily be removed or added in order to create the different research conditions.

Before the start of the intervention, participants choose which behaviour they want to improve. Participants are free to select either PA or SB. The structure of MyPlan 2.0 is the same for both PA and SB. After behaviour selection, the allocation to one of the research groups takes place. After being allocated into a research group, users will receive different website links to the corresponding interventions.

#### The website

The flow of the website is depicted in Figs. 1 and 2. In the first website session, users start with a short registration procedure, in which they have to register with their email address. They also have to fill in some demographic information, such as name, age and sex. Thereafter, they are offered the possibility to take a quiz. Via quiz-like questions, participants are provided with general information on the consequences and benefits of the selected behaviour (see Additional file 1). Then, all participants have to fill out either the short version of the ‘International Physical Activity Questionnaire’ (IPAQ) or the Last 7-days Sedentary Behaviour Questionnaire (SIT-Q-7d) (based upon their chosen behaviour) [54, 55]. Based on the answers in this questionnaire, users receive tailored feedback: their current level is compared to the health guidelines and suggestions are made on how they can improve their behaviour (e.g. in which domains). In order to guide them through actual behaviour change, users receive various behaviour-change components, according to the research condition they are assigned to.

**Fig. 1 Fig1:**
[figure not shown]
Flow of the first session on the website

**Fig. 2 Fig2:**
[figure not shown]
Flow of follow-up sessions 2, 3, 4 and 5 on the website

Users who receive *the action planning component* can start making their own plan for behaviour change by specifically defining what they are going to do, when and where. Various examples are provided and success stories of other users are shown as well.

*The coping planning component* is implemented by letting users choose which barriers they believe they will experience and providing a list of possible solutions for each of these barriers. Users can also provide other barriers and suggest their own solutions. Examples of how to create good coping plans are given.

In *the self-monitoring component*, users are prompted to self-monitor their goal. They are prompted to do this via the app, but they can also select other options (such as writing it down in their diary or on their calendar). A calendar page on which they can easily indicate their progress can be downloaded from the website.

Finally, a summary is shown of the action plan, and/or coping plan, and/or the plan to monitor this. Note that the content summary will vary as a function of the experimental condition. Users get the possibility to print this summary. Next, they can read about how social support can be elicited (e.g. talking to their partner, informing colleagues of their plan, using social platforms …).

In the subsequent four sessions on the website, users reflect on the process of behaviour change during the past week. They can maintain or adapt the action plan, coping plan and/or their self-monitoring method. Each week, extra tips and tricks to enhance behaviour change are added to the intervention content in order to optimally engage and support the users. Screenshots of the website can be found in Additional file 1.

#### The mobile application

The app of MyPlan 2.0 is synchronised with the website and provides user support on a daily basis. The included self-regulation techniques differ as a function of the experimental group (the app system recognises the email address and the user will get the app version of the group they are assigned to). *The action planning component* is implemented in the app by providing users with the option to change their plan throughout the week. Furthermore, the app reminds users of their plan by sending a message on the scheduled moment. For example, if a user planned to go for a walk on Tuesday, they receive a notification on Tuesday morning as a reminder. In *the coping planning component*, users can select barriers and receive an overview of possible solutions. If users are assigned to *the self-monitoring component*, a notification is sent at the end of each day, in which users are asked to what extent they succeeded in their plan (i.e. a score ranging from 1 ‘not succeeded’ to 5 ‘very well succeeded’). The scores are displayed in a graph and can be accessed in the self-monitoring module. If a user indicates a score of less than 3, they receive the advice to go to the coping planning component. Additionally, the app aims to engage users via elements of gamification (i.e. ‘the use of game design elements in non-gaming contexts’ [56], p.9) such as quizzes and collecting medals for completing website sessions or self-monitoring measures. Screenshots of the application can be found in Additional file 2.

### Participants

This study targets adults in the general Belgian population. The following inclusion criteria will be taken into account: (1) being ≥ 18 years old, (2) Dutch-speaking, (3) having Internet access and (4) being the owner of a smartphone. Before entering the study, people have to complete the ‘Physical Activity Readiness Questionnaire’ (PAR-Q) [57] which is a screening instrument to detect individuals at risk for adverse effects when being more physically active. The PAR-Q is a self-report instrument consisting of seven items to be answered by ‘yes’ or ‘no’. Participants will be excluded when one item or more will be endorsed. Participants receiving concomitant care or other interventions will not be excluded.

A convenience sample will be attained by recruiting possible participants in the city library of Ghent (i.e. ‘De Krook’), in city halls and shopping malls. Also participants will be recruited by social media, contacting participants of previous studies who indicated as having interest in other research, recruiting acquaintances and students, and applying snowball sampling.

Based on the meta-analysis of Conn et al. (2011) [58], we would like to be able to observe a small effect size of 0.19. To detect within- and between-subjects effects under significance level alpha = 0.05, and with a power of 0.80, a sample of 260 participants is needed. However, we will aim to recruit approximately 480 participants to take attrition into account. As such, an attrition rate of 46% of the participants is acceptable within this study, which seams feasible to the researchers. This is because actions to decrease drop-out were taken; no extensive questionnaires were used in MyPlan 2.0 in contrast to previous research (e.g. MyPlan 1.0) and, furthermore, the programme was adapted to increase user engagement based on both qualitative and quantitative research [46, 47].

The participants will be randomly allocated to eight equal groups (60 participants within one group). The randomisation will be done by the author of this study. Before recruitment of participants, blocked randomisation will be used to form an allocation list for the eight different groups. A computer random number generator (http://www.randomization.com) [59] with a block size of 40 will be used to assign the group numbers in random order within each block. The allocation list will be concealed for the researcher during the recruitment of participants. Each time a participant completes a pre-test measurement (at the library, city hall, shopping mall or at home; see Fig. 4) an automatic email will be sent to the researcher. After receiving this email, the participant will be allocated to the next number on the allocation list and will consequently be assigned to a group. By doing this, the allocation will be concealed until participants are enrolled and assigned to the intervention [60]. After assignment, the researcher will not be blind for the allocated intervention: the researcher will send participants different website links to their corresponding intervention. The participants on the other hand will not be aware of the different conditions of the study: they will only receive one website link (corresponding with their intervention).

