## Discussion

There is a need for effective e- and m-health interventions that enhance behaviour change. Additionally, e- and m-health interventions need to be relevant, time-efficient and engaging. This study may contribute to a further understanding of how, why and for whom interventions work. By investigating the role of various behaviour-change techniques and determinants of behaviour change, we will be able to provide guidance for the development of future e- and m-health interventions. One of the strengths of this study is its experimental and longitudinal design, allowing us to isolate the effects of the separate behaviour-change techniques. To our knowledge, the influence of behaviour-change techniques has only been investigated as a combined effect or in a non-experimental way [53, 82, 83] and many authors in the field refer to the need for an experimental design [33–35]. Another strength of the study is the fact that not only PA and SB are measured via self-reports, but also a range of determinants is measured at different points in time, i.e. pre, post, at follow-up and during the intervention. This allows a thorough analysis of the processes of behaviour change that interventions can target. The results of such analysis can inform future interventions on how to tailor behaviour-change techniques to different participants in various phases of behaviour change. This study should provide a large and rich dataset to explore these research questions in detail. However, the study also has some limitations. First, PA and SB are measured by self-report questionnaires (IPAQ or SIT-Q-7d), which may lead to response and recall biases [84]. Future research may consider the use of objective measures of PA and SB. Second, to lower the burden for participants and thus preventing attrition, each determinant of behaviour change will be measured via only three items, which can compromise the reliability and validity of the measurement. However, the items that are included were iteratively constructed and validated by experts in health psychology. Third, the size of the groups will not allow us to draw conclusions about the three-way interactions. However, we are more interested in the main effects and the two-way interaction effects. Fourth, because participants can freely choose either to improve their PA or to reduce their SB, we cannot ensure that both versions of the programme will have the same number of participants. Lastly, due to attrition, it is possible that the sample size between groups will differ. Therefore, it will be important to focus on keeping the participants in the study via the use of email reminders and telephone calls.

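### The 260 participants said to give 80% power for an effect of 0.19 do not do so for a technique main effect if 0.19 is a standardised mean difference

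*Protocol article*

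**What the plan says.** The sample-size text is in the Participants section of the protocol article. It draws its effect size from a cited meta-analysis: "we would like to be able to observe a small effect size of 0.19". It continues "To detect within- and between-subjects effects under significance level alpha = 0.05", and "with a power of 0.80, a sample of 260 participants is needed". Recruitment is set higher: "we will aim to recruit approximately 480 participants to take attrition into account", from which the article concludes that "an attrition rate of 46% of the participants is acceptable within this study".

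The same section allocates participants to eight equal groups, and Study design describes a 2 x 2 x 2 factorial. Data management and statistical analysis plans a two-level mixed model on physical activity and sedentary behaviour scores converted to z-scores. The Discussion concedes that group size will not support conclusions on three-way interactions, then adds: "However, we are more interested in the main effects and the two-way interaction effects".

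The article does not say whether 0.19 is a standardised mean difference or Cohen's f, which contrast or test was powered, how many measurements entered the calculation, or what correlation was assumed.

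**The concern.** Four numbers are offered as belonging together: effect 0.19, alpha 0.05, power 0.80 and N = 260. In a balanced factorial the whole sample serves each main effect, so this is the most favourable contrast available. Even so, a difference of 0.19 SD between two halves of 260 is small relative to its standard error.

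What is at stake is how the results are read. The Background presents the study as guidance on which techniques could be taken out of future interventions, so non-significant main effects will matter as much as significant ones. A reader who trusts the 80% will take a non-significant result as fairly strong evidence against an effect of 0.19 SD, when the chance of detecting such an effect may have been a third to about 70%.

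**Working it through.** **Inputs from the article.** Effect 0.19; alpha 0.05; power 0.80; N = 260; eight equal groups; z-scored outcome.

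**Assumptions, not in the article.** Two-sided test; outcome SD of 1; 0.19 as a standardised mean difference d (the alternative is tested in step 5); a common within-person correlation rho of 0.5 to 0.7 between measurements; physical activity and sedentary behaviour measured at PRE, POST and follow-up.

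**1. Trying to reproduce 260.** For a half-versus-half contrast, SE = 2·√(v/N), so N = 4v(1.96 + 0.8416)²/d². Here (1.96 + 0.8416)² = 7.849 and d² = 0.0361. The variance factor v is:
- POST only: v = 1
- baseline-adjusted POST: v = 1 − rho²
- baseline-adjusted mean of POST and follow-up: v = (1 + rho)/2 − rho²

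At rho = 0.5 these are 1, 0.75 and 0.50. The required totals are 4 × 1 × 7.849/0.0361 = 870, then 652 and 435. None is 260.

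**2. Power at 260 (130 v 130) for d = 0.19.** Power ≈ Φ(0.19/SE − 1.96).

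| Analysis | rho | v | SE | 0.19/SE | Power |
|---|---|---|---|---|---|
| POST only | – | 1 | 0.124 | 1.53 | 33% |
| Adjusted POST | 0.5 | 0.75 | 0.107 | 1.77 | 42% |
| Adjusted POST | 0.7 | 0.51 | 0.089 | 2.15 | 57% |
| Adjusted mean of POST and follow-up | 0.5 | 0.50 | 0.088 | 2.17 | 58% |
| Adjusted mean of POST and follow-up | 0.7 | 0.36 | 0.074 | 2.55 | 72% |

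**3. Correlation needed for 80%.** Setting N = 260 gives v = 260 × 0.0361/(4 × 7.849) = 0.299. With one post measure, 1 − rho² = 0.299 gives rho = 0.84. With two, (1 + rho)/2 − rho² = 0.299 gives rho = 0.76.

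**4. Detectable main effect at 260 with 80% power.** 2.8016 × SE: 0.35 SD (POST only), 0.30 SD (adjusted POST, rho 0.5) and 0.25 SD (adjusted mean of POST and follow-up, rho 0.5).

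**5. The alternative metric.** Take 0.19 as Cohen's f in a repeated-measures ANOVA with eight groups, between-subjects test, assumed rho 0.5, and noncentrality N·f²·m/(1 + (m − 1)·rho) for m measurements. The total N for 80% is 273, 256 and 246 for m = 3, 4 and 5. These values bracket 260. For a two-level factor d = 2f, so f = 0.19 means d = 2 × 0.19 = 0.38. A single-degree-of-freedom main effect of that size needs about 220, and at 260 it has 86% power on POST alone.

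**6. Two-way interactions.** Written as a difference of differences, the SE is 4·√(v/N), twice that of a main effect. For 0.19 SD at N = 260 power is 12% (POST only), 14–19% (adjusted POST, rho 0.5–0.7) or 19–25% (adjusted mean of POST and follow-up, rho 0.5–0.7).

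**7. Attrition step.** 1 − 260/480 = 45.8%, which matches the stated 46%.

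**The case against.** The strongest reply is that the metric is not stated and the cited meta-analysis is not available here, so the arithmetic cannot be called wrong outright. The reference to within- and between-subjects effects suggests a repeated-measures ANOVA calculation, and with f = 0.19 and eight groups such a calculation lands on either side of 260. Nor does the word small settle the metric, since 0.38 SD lies between the usual small and medium benchmarks. This stands as far as it goes: the 80% may be correct for a target of 0.38 SD. It does not rescue the paragraph for a reader who takes 0.19 as the difference to be detected in SD units, and nothing in the text warns that reader.

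A second reply is that a journal article need not print its software settings. That is fair, and missing settings alone would be no finding. Here, however, the article chose to state effect, alpha, power and N, and on the natural reading they do not fit together.

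Third, a mixed model and multiple imputation may recover information from participants who drop out. With all 480 measured, the adjusted mean of POST and follow-up at rho 0.5 would have 84% power for 0.19 SD. But the article attributes its 80% to 260, so this does not support the sentence as written.

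Stronger criticisms are tempting but not supported:
- A reader might infer that the attrition allowance is wrong because the Background reports that "high attrition rates (60–80%) are observed" in this field. The article gives reasons for expecting less loss in this programme, and its division is correct.
- A reader might infer that interactions certainly have very low power. That depends on definition: under effect coding at the same standardised size, interaction power equals main-effect power.
- A reader might infer that non-significant techniques will be declared removable. The article contains no such rule.

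**Conclusion.** The point holds conditionally. If 0.19 is a standardised mean difference, as a small meta-analytic effect analysed on z-scores suggests, 260 analysed participants give about 33% to 72% power for a technique main effect, depending on the analysis and on a correlation up to 0.7. The stated 80% would require a correlation of about 0.84 with one post measure or 0.76 with two. If 0.19 was entered as Cohen's f, 260 is of the right order, but the effect covered at 80% power or more is 0.38 SD, double the face value. Either way the paragraph needs correcting or clarifying.

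A reader might quote one low power figure as a fact about this trial. The documents do not support that, because both the metric and the correlation are assumptions here. The interaction figures in step 6 carry the further condition that the effect is a difference of differences.

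**What to change.** In the sample-size paragraph of the Participants section:

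1. Name the metric of 0.19, the contrast it refers to, the number of measurements and the assumed within-person correlation.
2. Replace the claim of 80% power for 0.19 with what 260 delivers: either the power under the stated assumptions, or the detectable main effect (about 0.35 SD on POST alone; 0.30 SD for baseline-adjusted POST and 0.25 SD for the adjusted mean of POST and follow-up, the latter two at rho 0.5). If 0.19 was Cohen's f, say so and give the equivalent difference of 0.38 SD.
3. State that two-way interactions, expressed as a difference of differences of the same size, have much lower power (about 12–25% for 0.19 SD at rho 0–0.7).
4. Report main effects and two-way interactions with confidence intervals, so that a non-significant result is not read as a null obtained with 80% power.

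The cost is wording only. No extra recruitment is asked for. The price is a less favourable power statement.
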